### Randomization

After confirmation of eligibility and baseline assessments (t0), patients will be randomized using Internet software (www.sealedenvelope.com), in a 1:1 ratio to the supervised exercise group (intervention group) or the usual care group (control group), using a permutated block design with random block sizes (4, 6, 8) with stratification by two dichotomous variables, which are known risk factors for ARC:Age (< 50 years or older)Receiving anti human epidermal growth factor receptor 2 (anti-HER2) therapy (yes/no)

This process will be performed by an external individual who is blinded to the study and who will place the sequence in a numbered, opaque, sealed envelope. The allocation of participants will then be reported to an oncologist (AJ) who will subsequently inform the patients about the assignment group.

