### Sample size calculation

The sample size was determined by a power calculation based on resting LVEF outcome, using a non-commercial statistical power analysis program (G*Power Version 3.1.9.2). Based on an effect size of 0.6 for resting LVEF presented in a previous study [26], to ensure statistical power of 80% and a significance level of 0.05, using the *t* test for two independent groups, the recruitment of 72 participants is required. Predicting a 20% dropout rate [19], we estimate that a total of 90 patients will be needed (45 in each arm). There are no planned early stopping rules. Adverse events will be evaluated by the study investigators, who will make the decision to stop the study early if there is a clinically relevant increased risk.

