### Statistical analyses

Statistical data analysis will be performed using the Statistical Package for the Social Sciences. The statistical significance will be set at a *p* value <0.05. Intention-to-treat and per-protocol approaches will be used both for all analyses. Data analysis will start with standard descriptive methods to describe the data (means and standard deviations will be calculated for continuous variables and absolute and relative frequencies for categorical variables).

Continuous variables will be compared between the two study groups using one-way analysis of covariance (ANCOVA), adjusted for the effect of the baseline values (covariate). A linear two-way mixed ANCOVA model with repeated measures (t1, t2 and t3) will be performed to test the difference over time between the two study groups and interaction (Group × Time), on primary and secondary outcomes, with the same covariate as the one-way ANCOVA. Bonferroni’s post-hoc procedure will be performed to locate the pairwise differences. Normality will be verified by the Kolmogorov-Smirnov test and the homogeneity of the variance will be validated by Levene’s test. Effect size will be calculated to estimate variance between moments through partial eta-squared. The cutoff values were defined as 0.02 for small effect size, 0.13 for moderate, and 0.26 for large effect sizes [36]. The chi-squared test will be used to check for a relationship between categorical variables. The effect size will be calculated using Cramer’s V test and interpreted based on the following cutoff values: 0.10 for a small effect, 0.30 for a medium effect, and 0.50 for a large effect. [36] No interim analyses will be conducted.

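### The 72-patient requirement is a one-sided figure; two-sided, 72 evaluable patients give about 71% power by the t test used for sizing, not 80%

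*Protocol article*

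**What the plan says.** The Sample size calculation section of the protocol article bases the trial size on resting LVEF, one of three primary outcomes. It gives these inputs:

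- Effect: "Based on an effect size of 0.6 for resting LVEF presented in a previous study [26".
- Power and error rate: "to ensure statistical power of 80% and a significance level of 0.05".
- Method: a t test, "using a non-commercial statistical power analysis program (G*Power Version 3.1.9.2").
- Result: "for two independent groups, the recruitment of 72 participants is required".
- Inflation: "Predicting a 20% dropout rate [19], we estimate that a total of 90 patients will be needed (45 in each arm").

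The Randomization section sets equal allocation, so 72 means 36 per arm. Neither the sample size paragraph nor the Statistical analyses section says whether the test is one-sided or two-sided. The latter sets significance at p < 0.05 without a direction. It plans a one-way ANCOVA adjusted for baseline, a mixed repeated-measures ANCOVA with a Group × Time interaction, and Bonferroni pairwise comparisons.

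**The concern.** Every input needed to reproduce the sample size is printed except the sidedness of the test. An effect of 0.6 with 80% power at a two-sided 0.05 level needs clearly more than 36 per arm, so 72 suggests that the one-tailed option was used in the software. A one-sided 0.05 criterion corresponds to a two-sided criterion of p < 0.10, not to the non-directional p < 0.05 of the analysis section. Sizing and analysis would then rest on different error rates.

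At stake is how an LVEF result is read. LVEF is the only outcome behind the sample size, and the article's own Discussion reports that two earlier exercise studies, including the one that supplied the effect size, saw no relevant echocardiographic changes. A null LVEF result is therefore a realistic outcome, and it would be judged against a claimed type II error of 20% that the stated method does not deliver.

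**Working it through.** **Inputs.** From the Sample size calculation section: d = 0.6, power 0.80, α = 0.05, two-sample t test, 20% dropout. From the Randomization section: 1:1 allocation. Sidedness is not stated, so both versions are computed.

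**Formula.** With n per arm, the test statistic is noncentral t with df = 2n − 2 and noncentrality δ = d·√(n/2). One-sided power is P(T > t at 1 − α). Two-sided power is P(|T| > t at 1 − α/2). This is the exact calculation for a two-sample t test.

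**1. Reproducing the stated 72 (one-sided).** The requirement solves to n = 35.04, so 36 per arm and 72 in total. At n = 36, δ = 0.6 × √18 = 2.546 on 70 df, and power is 80.9%. This matches the protocol exactly.

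**2. The same inputs, two-sided.** The requirement solves to n = 44.59, so 45 per arm and 90 evaluable. The normal approximation gives 44 per arm, so the choice of method does not explain the gap of 18 patients.

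| Evaluable per arm | δ = 0.6·√(n/2) | One-sided power | Two-sided power |
|---|---|---|---|
| 36 | 2.546 | 80.9% | 70.9% |
| 45 | 2.846 | 88.1% | 80.4% |

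**3. Dropout.** 72 / (1 − 0.20) = 90, so the protocol's inflation step is right for its base. With the two-sided base, 90 / (1 − 0.20) = 112.5, so 113 randomised, or 114 for equal arms.

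**4. Detectable effect.** With 36 evaluable per arm, two-sided power reaches 80% at d = 0.67. Rounding of the effect size does not close the gap: d = 0.65 still needs 78 evaluable patients.

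**5. Allowing for the planned ANCOVA.** Adjustment for baseline with correlation r between baseline and outcome raises the standardised effect to d/√(1 − r²). The protocol gives no r, so the range below is an assumption. At 36 per arm, two-sided (keeping 70 df; the one df spent on the covariate is ignored):

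| r | 0 | 0.3 | 0.4 | 0.44 | 0.45 | 0.5 | 0.6 |
|---|---|---|---|---|---|---|---|
| Power | 70.9% | 74.9% | 78.2% | 79.8% | 80.3% | 82.6% | 88.1% |

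The threshold is about 0.45: 0.6/√(1 − 0.45²) = 0.6/0.893 = 0.672, which is the detectable effect from step 4.

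**The case against.** The strongest reply is that two-sidedness is inferred, since the protocol never uses the word. The Hypothesis section is directional: exercise is expected to limit the decline in cardiac function. A deliberate one-tailed setting is possible, and for that setting both 72 and 90 are computed correctly. It is also true that an article condenses a fuller protocol.

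This changes how the fault is described but does not remove it. A directional hypothesis does not declare a one-sided test, and the analysis section carries no direction into the F tests or the pairwise comparisons. Either the sizing should have been two-sided, or an undeclared one-sided level sits beside a non-directional analysis. The fault lies in a printed figure that does not fit the printed analysis, not in a detail left out.

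The second reply is that 70.9% belongs to the unadjusted t test, whereas the planned comparison is baseline-adjusted. This stands as a limit on the claim: power under the planned analysis may lie below or above 80%, depending on an unstated correlation. It cannot justify the 72, because the protocol names the t test as its sizing method and makes no use of the gain from adjustment.

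The third reply is that 90 randomised patients do give 80.4% two-sided. That requires no dropout at all, against the protocol's own prediction of 20%.

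**Conclusion.** The concern holds. The stated 72 reproduces only with a one-sided 0.05 level that the protocol does not declare. For a two-sided t test at 0.05, the requirement is 90 evaluable patients, so 90 randomised leaves no room for dropout on that method. With the predicted 20% dropout, two-sided power for d = 0.6 is 70.9%, about 9 points below the stated 80%; the type II error is 29%, not 20%.

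Two assumptions carry this: that unqualified p < 0.05 with ANCOVA F tests means a two-sided analysis, and that power is judged by the unadjusted t test named for sizing. Under the planned ANCOVA the shortfall disappears if the LVEF correlation is about 0.45 or higher, and persists in part below that. The error lies in the power statement; it does not bias the treatment estimate or inflate the false-positive rate of the planned analysis.

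**What to change.** Keep 90 randomised and rewrite the sample size paragraph, for example: *Two-sided significance level 0.05. Ninety patients will be randomised; with 20% dropout, 72 will be evaluable. By a two-sample t test this gives 71% power for an effect size of 0.6 and 80% power for 0.67. With the planned baseline-adjusted ANCOVA, power for 0.6 is 80% if the correlation between baseline and outcome LVEF is at least 0.45; this value is an assumption.* Add a source for the correlation if there is one, and state two-sided testing in the Statistical analyses section as well.

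If a one-sided test was intended, it has to be declared and justified, and the analysis section changed to match; the one-sided figure should not stay beside a two-sided analysis. If 80% power by the two-sided t test is to be kept after 20% dropout, 114 patients would have to be randomised.

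The preferred repair costs one corrected paragraph and no extra patients. The price is a less favourable power statement.

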### Statistical analyses

Statistical data analysis will be performed using the Statistical Package for the Social Sciences. The statistical significance will be set at a *p* value <0.05. Intention-to-treat and per-protocol approaches will be used both for all analyses. Data analysis will start with standard descriptive methods to describe the data (means and standard deviations will be calculated for continuous variables and absolute and relative frequencies for categorical variables).

Continuous variables will be compared between the two study groups using one-way analysis of covariance (ANCOVA), adjusted for the effect of the baseline values (covariate). A linear two-way mixed ANCOVA model with repeated measures (t1, t2 and t3) will be performed to test the difference over time between the two study groups and interaction (Group × Time), on primary and secondary outcomes, with the same covariate as the one-way ANCOVA. Bonferroni’s post-hoc procedure will be performed to locate the pairwise differences. Normality will be verified by the Kolmogorov-Smirnov test and the homogeneity of the variance will be validated by Levene’s test. Effect size will be calculated to estimate variance between moments through partial eta-squared. The cutoff values were defined as 0.02 for small effect size, 0.13 for moderate, and 0.26 for large effect sizes [36]. The chi-squared test will be used to check for a relationship between categorical variables. The effect size will be calculated using Cramer’s V test and interpreted based on the following cutoff values: 0.10 for a small effect, 0.30 for a medium effect, and 0.50 for a large effect. [36] No interim analyses will be conducted.

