### Limitations

There are some limitations to this study, which should be noted. First, we will only include patients followed at CHVNG/E. Second, due to the impossibility of blinding patients and some of the researchers to study group assignment, the open design of this study may influence the assessment retention rate of participants allocated to the control group. Third, we will stratify our sample based on age (under/over 50 years) and use of trastuzumab (yes/no). However, there are other risk factors associated with ARC, including total cumulative anthracycline dose, pre-existing cardiac disease, and treatment with mediastinal radiation, that should also be considered [19]. Although these hinderances should be acknowledged, we believe the findings from the present study will provide important data, which will be of relevance to the contemporary literature on this subject.

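### The repeated-measures ANCOVA, if run as the GLM procedure its wording suggests, turns the intention-to-treat analysis into a completers analysis under the predicted 20% dropout

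*Protocol article*

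**What the plan says.** All of this is in the protocol article.

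- **Analysis sets** (Statistical analyses): "Intention-to-treat and per-protocol approaches will be used both for all analyses".
- **Longitudinal model** (same section): "A linear two-way mixed ANCOVA model with repeated measures (t1, t2 and t3) will be performed", testing group, time and their interaction on primary and secondary outcomes, with the baseline value as covariate. A baseline-adjusted one-way ANCOVA is also named for continuous variables.
- **Accompanying procedures** (same section): Bonferroni post-hoc comparisons; "the homogeneity of the variance will be validated by Levene’s test"; "Effect size will be calculated to estimate variance between moments through partial eta-squared".
- **Software** (same section): "Statistical data analysis will be performed using the Statistical Package for the Social Sciences".
- **Dropout** (Sample size calculation): 72 participants are required, and a predicted 20% dropout raises this to 90, with 45 per arm.
- **Retention by arm** (Limitations): "the open design of this study may influence the assessment retention rate of participants allocated to the control group".
- **Visits** (Study assessments): outcomes are measured at t0, t2 and t3, with t3 three months after t2. Only NT-proBNP is also measured at t1, before each chemotherapy cycle.

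**The concern.** A between-within ANCOVA fitted by the GLM repeated-measures procedure needs every repeated level for every patient. A woman with an echocardiogram at t2 but none at t3 leaves the model entirely, and her t2 value goes with her. With one patient in five predicted to drop out, an analysis carrying the intention-to-treat label would describe only those who completed.

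The first cost is precision at t2, the end of the intervention. The second is exposure to attrition bias if the patients who leave differ between arms in a way related to how their hearts were doing. Both bear on LVEF and strain, two of the three primary outcomes, and on NT-proBNP, the third.

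**Working it through.** **1. The plan's own figure.** 72 / (1 − 0.20) = 90, which reproduces. The design therefore counts on 72 complete patients, and up to 18 of 90 randomised patients would be absent from a model that needs every visit. (The 72 itself comes from a one-sided t test: at d = 0.6 with 36 per arm, power is 80.9% one-sided and 70.9% two-sided. The article does not state sidedness. That is a separate matter.)

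**2. Which procedure is named.** A two-way mixed design with a Group × Time test, Bonferroni comparisons, Levene's test and partial eta-squared in SPSS matches the output of GLM repeated measures. A likelihood mixed model would normally come with a covariance structure or random effects, and neither is mentioned. This is a strong inference, not a statement in the text.

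**3. How many t2 values are lost.** The article does not say when dropout occurs, so the split is assumed. In each row 90 × 0.80 = 72 patients have t3.

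| Lost by t2 | Lost by t3 | t2 observed | t2 values discarded |
|---|---|---|---|
| 20% | 20% | 72 | 0 |
| 10% | 20% | 81 | 9 (9/81 = 11%) |
| 0% | 20% | 90 | 18 (18/90 = 20%) |

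**4. Precision at t2 under random loss.** Assume a correlation of 0.6 between visits. The residual SD given baseline is √(1 − 0.6²) = 0.8. The standard error of the arm contrast is about 0.8 × √(2/n per arm):
- all 45 per arm: 0.8 × √(2/45) = 0.169 SD;
- 36 completers per arm: 0.8 × √(2/36) = 0.189 SD.

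The ratio is √(45/36) = 1.118, or about 12% more. Simulation agrees (0.173 against 0.194 SD in one run). For the 10%/20% split the ratio is √(81/72) = 1.061. For the average of t2 and t3, simulation gives 0.161 SD for completers against 0.149 SD with all observed data.

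**5. Bias.** Simulation with no true effect, 45 per arm, correlation 0.6, baseline and t2 observed for all, and loss before t3. The completers ANCOVA is compared with an estimator using all observed data.

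| Loss pattern | Completers bias, t2 | Completers bias, t3 | Bias and two-sided type I error, t2–t3 average |
|---|---|---|---|
| 20% at random, both arms | 0.00 | 0.00 | 0.00; about 5% |
| 30% control, 10% intervention, at random | 0.00 | 0.00 | 0.00; about 5% |
| About 30% control, depending on baseline; 10% intervention, at random | 0.00 | 0.00 | 0.00; about 5% |
| About 21% in both arms, same dependence on t2 | 0.00 | 0.00 | 0.00; about 5% |
| About 30% control, depending on t2; 10% intervention, at random | −0.16 to −0.22 | −0.06 to −0.09 | −0.11 to −0.15; 11% to 16% |

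The ranges in the last row cover a log-odds of dropout rising by 1.0 to 1.5 per SD of poorer t2 value. The all-data estimator has bias of about 0.00 in every row. The negative sign means bias against exercise, and follows from assuming that controls with poorer values leave. The opposite assumption reverses it.

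**6. NT-proBNP.** Over the three named levels, at an assumed 5% missing per level, 0.95³ = 0.857, so about 14% of patients would be excluded.

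**The case against.** The article nowhere says that incomplete patients are excluded, and imputation followed by ANCOVA would be compatible with its wording. Levene's test could belong to the one-way ANCOVA in the same paragraph. Intention-to-treat, set beside per-protocol, may mean only that patients are analysed in their assigned arm. Missing-data handling is commonly left to an analysis plan that is not shown, and raising 72 to 90 is routine sizing. The investigators also plan reminders and will record reasons for withdrawal where possible.

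Much of this stands. The exclusion is inferred, and the absence of a missing-data rule is not in itself a fault. What remains is that the article does name a model, and the natural reading of that model handles incomplete patients poorly. Reminders may reduce the loss but do not change what the model does with it.

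A reader might infer more than the documents support:

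- *That the plan expects control-arm loss.* The Limitations section says only that the open design may affect control retention. It gives no figure and no link to outcome.
- *That 20% dropout, or unequal dropout, biases the result.* Loss that is random, or that depends only on arm and baseline, leaves the baseline-adjusted contrast unbiased.
- *That every analysis discards partial follow-up.* The one-way ANCOVA at t2 keeps patients lost only at t3.
- *That NT-proBNP would lose far more than 14%.* That requires each pre-cycle draw to be its own level, whereas the model names three levels and the article gives no number of cycles.

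**Conclusion.** The point holds as a weakness in the chosen method and should be corrected. If the repeated-measures ANCOVA is the GLM procedure without imputation, it analyses about 72 of 90 randomised patients under an intention-to-treat label. The certain cost is precision at t2: between nothing and about 12% on the standard error, according to how much of the 20% loss falls after t2, assuming random loss balanced between arms. Bias is conditional. It requires loss that differs by arm and depends on post-baseline outcome. The documents do not predict this, but they do not exclude it. In the illustrative case the bias averaged over t2 and t3 is 0.11 to 0.15 SD, about a fifth to a quarter of the 0.6 design effect (0.11/0.6 = 18%; 0.15/0.6 = 25%). These sizes rest on the assumed correlation, dropout timing and dropout mechanism.

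**What to change.** Replace the repeated-measures ANCOVA with a likelihood-based linear mixed model (SPSS MIXED):

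- **Visits:** those at which each outcome is measured: t2 and t3 for LVEF and strain, plus the t1 draws for NT-proBNP. The draw before the first cycle precedes exercise and should not count as post-baseline.
- **Covariance:** unstructured, with a prespecified simpler structure for NT-proBNP if needed.
- **Fixed effects:** arm, visit, arm × visit, baseline, baseline × visit, and the two stratification factors (age group and anti-HER2 therapy).
- **Patients:** every randomised patient with at least one post-baseline value, in the assigned arm. Report by arm how many have none.
- **Result:** the arm contrast at t2 and at t3, with confidence intervals.
- **Sensitivity:** keep the completers ANCOVA.

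If a likelihood-based model was already intended, one sentence saying so and naming the covariance structure is enough.

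The cost is a change of wording and slightly more analysis work in software already named, with no new data. The model still assumes data missing at random, so it does not protect against loss driven by unobserved outcomes.

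### Randomisation is stratified by age and anti-HER2 therapy, but both ANCOVA models adjust for baseline only; if these factors predict the outcome beyond baseline, the reported standard error is too wide and some power is lost

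*Protocol article*

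**What the plan says.** The Randomization section of the protocol article allocates patients "in a 1:1 ratio to the supervised exercise group (intervention group") or usual care, "using a permutated block design with random block sizes (4, 6, 8"), and "with stratification by two dichotomous variables, which are known risk factors for ARC". The factors are age (under 50 or older) and "Receiving anti human epidermal growth factor receptor 2 (anti-HER2) therapy (yes/no"), which gives four strata. The Limitations section repeats the stratification.

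The Statistical analyses section compares continuous variables between groups by one-way ANCOVA, "adjusted for the effect of the baseline values (covariate"). A two-way mixed ANCOVA with repeated measures follows for the primary and secondary outcomes, "with the same covariate as the one-way ANCOVA". No section places age group or anti-HER2 therapy in any analysis model.

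The covariate set is stated, in the singular, and reused for the second model. It is therefore a choice the document makes, not a detail it leaves open.

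**The concern.** Stratified permuted blocks balance the arms on the two factors, so the factors contribute little to the chance variation of the treatment difference. If the model omits them, whatever variance they explain stays in the residual term. The model then reports a standard error larger than the true sampling variation of the estimate. Confidence intervals are too wide and the test rejects less often than its nominal level.

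The protocol's own rationale makes this plausible. The factors were chosen as risk factors for cardiac deterioration under treatment, and the primary aim concerns change in NT-proBNP, longitudinal strain and LVEF. A factor that drives deterioration can predict the post-treatment value even after adjustment for the baseline value. At stake is the precision of the primary comparisons, not their validity.

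**Working it through.** **Inputs from the documents.** Allocation 1:1; two binary stratification factors; blocks of 4, 6 and 8; standardised effect 0.6 for LVEF; 80% power; significance level 0.05, sidedness not stated; t test for two independent groups; 72 evaluable patients (36 per arm); 20% dropout; 90 in total.

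**Assumed.** R², the share of the outcome variance left after baseline that the two factors explain together: 0 to 0.20. The effect of 0.6 is taken in units of the SD left after baseline adjustment. The test is taken as two-sided unless stated.

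**The plan's own figure.** Noncentral-t power for two independent groups at effect 0.6:
- one-sided 0.05: 36 per arm, total 72, power 80.9%; 72 / (1 − 0.20) = 90. This matches the protocol.
- two-sided 0.05: 45 per arm, total 90 before dropout. With 36 per arm, power is 70.9%.

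So 72 reproduces with a one-sided test. The two-sided results below start near 71% for that reason and not because of the covariate set.

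**Formula.** If the factors explain R² of the residual variance, the residual SD falls by √(1 − R²) once they are in the model. The reported standard error without them, relative to that with them, is 1/√(1 − R²). The noncentrality with adjustment is 0.6 × √(36/2) / √(1 − R²) = 2.546 / √(1 − R²); for example 2.546/0.949 = 2.68 at R² = 0.10. Degrees of freedom are 70 without the factors and 68 with them (the one for baseline is ignored).

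| R² | SE overstated by | Two-sided power with factors | One-sided power with factors |
|---|---|---|---|
| 0 | 0% | 70.9% | 80.9% |
| 0.02 | 1.0% | 71.7% | 81.6% |
| 0.05 | 2.6% | 73.1% | 82.7% |
| 0.10 | 5.4% | 75.3% | 84.4% |
| 0.15 | 8.5% | 77.7% | 86.2% |
| 0.20 | 11.8% | 80.1% | 88.0% |

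The R² = 0 row also shows that the two extra degrees of freedom cost practically nothing.

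**Simulation.** Subtracting 70.9% from the two-sided column slightly overstates the gain, because stratification also steadies the unadjusted estimate. The comparison was therefore simulated: 72 patients, stratified permuted blocks of 4/6/8, 45% under 50 and 20% on anti-HER2 therapy (both assumed), R² split equally between the factors, two-sided 0.05, 8,000 trials per setting.

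| R² | Type I error, baseline only | Type I error, with factors | Power, baseline only | Power, with factors |
|---|---|---|---|---|
| 0 | 5.0% | 5.0% | 70.2% | 70.0% |
| 0.05 | 4.6% | 5.1% | 70.2% | 71.9% |
| 0.10 | 4.3% | 5.2% | 70.3% | 74.0% |
| 0.20 | 2.8% | 4.6% | 71.9% | 79.6% |

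With 50% under 50 instead of 45%, a separate simulation of 6,000 trials per setting gives power rising from 71% to 73%, 71% to 75% and 74% to 81% at R² = 0.05, 0.10 and 0.20, with unadjusted type I error of 4.7%, 3.9% and 2.9%.

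**Where the loss sits.** In that second simulation, at R² = 0.20, the baseline-only model reports a mean standard error of 0.235 while the estimate actually varies with SD 0.214. With the factors the two agree: 0.210 and 0.211. The estimate itself is almost as precise either way (0.214 against 0.211). What goes wrong is the reported uncertainty.

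**The case against.** **The effect is conditional.** If the factors predict nothing beyond baseline, nothing is lost. The Background section gives a definition of cardiotoxicity based on a fall in LVEF past a threshold. Being a risk factor for that event does not show how much variance a factor explains in baseline-adjusted continuous LVEF, strain or NT-proBNP. This stands, and the point is worded accordingly.

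**The upper end is demanding.** With 50% under 50, 20% on anti-HER2 therapy and R² = 0.20 split equally, anti-HER2 therapy must shift the outcome by √(0.10/0.16) = 0.79 residual SD and age group by √(0.10/0.25) = 0.63, each more than the assumed treatment effect of 0.6. At R² = 0.05 the shifts are 0.40 and 0.32 and the gain is about 2 points. The lower half of the range is the safer expectation.

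**Stronger readings that a reader might infer.** One is that the stratification is wasted. It is not: balance is kept and the estimate retains nearly all of the precision gain; only its standard error is overstated. Another is that the loss falls on a trial already below its stated power. The documents do not establish this. Sidedness is not stated, and 72 patients give 80.9% with a one-sided test. Nor is the scale of the 0.6 stated: on the raw SD scale, baseline ANCOVA at 36 per arm would give about 75%, 83% or 88% two-sided power at assumed baseline correlations of 0.3, 0.5 or 0.6.

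**Validity is not affected.** There is no bias, and the only error is conservative, so a significant result would stand. This is correct and limits the weight of the point.

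**Scope.** The stated rationale for the factors is ARC. It gives no ground for expecting a loss on grip strength, sit-to-stand or self-reported activity.

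**Conclusion.** The mismatch between design and analysis is real and is written into the document. Its consequence is conditional and of unknown size: a reported standard error too wide by 2.6% at R² = 0.05, 5.4% at 0.10 and 11.8% at 0.20, with power gains from adjustment of about 2, 3 to 4, and 7 to 8 points respectively, and none at R² = 0. These gains assume 72 evaluable patients, a two-sided 0.05 test, an effect of 0.6 on the post-baseline SD and the assumed stratum frequencies. On a one-sided test the formula gives similar gains (1.8, 3.5 and 7.1 points from 80.9%). This is a matter of efficiency and correct standard errors. It does not threaten the validity of a positive finding, and it is worth correcting mainly because the correction is nearly free.

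**What to change.** In the Statistical analyses section, state that the one-way and the repeated-measures ANCOVA include age group (under 50 or older) and anti-HER2 therapy (yes/no), as recorded at randomisation, as fixed covariates beside the baseline value. Apply this at least to NT-proBNP, LV global longitudinal strain and LVEF; extending it to the other outcomes is optional and can be done for uniformity. Make the change before any outcome data are examined by group, so that the adjustment is prespecified. The cost is one sentence and two degrees of freedom. No new data are needed, since both factors must be known before a patient can be randomised.
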